### **Part C (SAD and/or MAD), Adaptive Cohorts 11-15**

Based on available safety, PK, and/or PD data from Part A and Part B (if applicable), doses for Part C (optional, adaptive Cohorts 11-15) will be chosen up to a total daily dose of 50 mg. The frequency of dosing (QD or twice daily [BID]), duration of dosing (single on one day or multiple over 14 days), and fasting versus fed status may also be modified versus Parts A and B. If dosing is administered in the fed state, standard meal conditions may also be modified at sponsor discretion. QD doses will be administered in the morning following a standard meal, and BID doses will be administered after a standard morning meal and evening snack, with the second dose administered 12 hours ( $\pm$  10 minutes) after the morning dose. Once determined, dose level, duration of dosing, frequency of dosing, and meal conditions will remain consistent within a cohort. For any multiple-dose cohort in Part C with BID dosing, both morning and evening doses must be administered on Day 14.

Within each cohort, 10 unique subjects will be randomized 4:1 to receive up to a total daily dose of 50 mg TLC-2716 (N = 8) or PTM (N = 2) for either 1 day (as in Part A) or 14 days (as in Part B). Adaptive, multiple-dose cohorts in Part C may be initiated in parallel with previous cohorts if the total daily dose under evaluation is at or below a dose already evaluated in Part B. If doses chosen in 2 or more adaptive cohorts exceed the dose evaluated in a previous cohort in Part B, these cohorts will be conducted in a staggered manner (lowest dose first), with the same stopping criteria as detailed in Section 3.3. Additionally, if the total daily dose in any cohort in Part C is greater than has been evaluated in any prior cohort, then sentinel dosing including one subject randomized to placebo and one subject to TLC-2716 will be included. Randomization of the remaining eight subjects in the cohort will be based on evaluation of all safety and tolerability data through Day 2 for these two sentinel subjects.

The sponsor, in consultation with the investigator, may choose not to initiate any or all adaptive cohorts if deemed unnecessary.

The cohorts and study treatments for Part C are as follows:

| Cohort | Day -1a   | Single Dose (Day 1) or Multiple Doses (Days 1-14)                                 |

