### 1.2.3. Nonclinical Pharmacokinetics (PK)

Absorption, distribution, metabolism, and elimination of TLC-2716, as well as the potential for drug-drug interactions, were assessed *in vitro* and *in vivo* in preclinical models. The pharmacokinetic (PK) profile indicates limited systemic exposure, with undetectable plasma levels 2-4 hours after dosing, and high levels in the liver consistent with rapid transporter-mediated uptake into hepatocytes.

TLC-2716 is a lipophilic, small molecule, LXR inverse agonist with a high binding affinity to plasma proteins (> 99%) in humans, mice, rats, dogs, and monkeys. Following intestinal absorption into the portal vein, TLC-2716 is highly extracted by the liver (92% hepatic extraction ratio in rats). Consistent with high liver loading, systemic exposure of TLC-2716 was generally low following oral administration in multiple species. In rodents, TLC-2716 was predominantly distributed to the liver and intestine; brain distribution data suggest that little or no TLC-2716-derived compounds cross the blood-brain barrier. *In vitro*, TLC-2716 was stable in primary hepatocytes from human, mouse, and dog. Together with the metabolites observed in

livers from preclinical species *in vivo*, the biotransformation pathway of TLC-2716 appears to involve oxidation, deamination, desulfation, glucuronidation, and taurine conjugation.

In *in vitro* studies, TLC-2716 was not a substrate of CYP1A2, CYP2B6, CYP2C8, CYP2C9, CYP2C19, CYP2D6, or CYP3A5, however, it was a modest substrate of CYP3A4 suggesting that co-administration of CYP3A4 inhibitors or inducers may affect the exposure of TLC-2716. TLC-2716 did not inhibit CYP1A2, CYP2C19, or CYP2D6, but demonstrated weak to modest inhibition of CYP2B6, CYP2C8, CYP2C9, and CYP3A4. In primary human hepatocytes, TLC-2716 induced CYP2B6 and CYP3A4 (> 2-fold relative to control), and therefore, may alter the exposures of co-administered substrates of these CYP enzymes *in vivo*. Finally, inhibition of P-gp, BCRP, OATP1B1, and OATP1B3 by TLC-2716 was observed *in vitro* at 10  $\mu$ M. While these findings suggest that TLC-2716 may alter the exposure of concomitant medications (and vice versa), the unique PK profile of TLC-2716, characterized by minimal systemic exposure and high protein binding, may reduce the potential for clinically relevant drug-drug interactions. Additional studies will be conducted to evaluate the clinical relevance of these findings.

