### 3.1.3. Part C: Adaptive SAD and/or MAD (Cohorts 11-15)

Part C includes optional, adaptive cohorts to evaluate the safety, tolerability, PK, and PD of single- and/or multiple-ascending doses of oral TLC-2716 or placebo under fasted or fed conditions. Based on available safety, PK, and/or PD data generated in Part A and Part B, as applicable, doses for Part C (Cohorts 11-15) will be chosen, up to a total daily dose of 50 mg. Planned study treatments within each cohort are provided in [Table 4](#).

Part C will proceed in up to 5 dose-escalation cohorts and will be governed by a review of safety, tolerability, and any available and relevant PK and/or PD data generated from previous Part A, B, and/or C cohorts, as applicable.

- Randomized, blinded (sponsor-unblinded), placebo-controlled, single- and/or multiple-ascending doses of TLC-2716 with adaptive dose selection in healthy subjects. An attempt will be made to enroll at least 3 subjects in each cohort with Screening TG  $\geq$  150 mg/dL and/or low-density lipoprotein cholesterol (LDL-C)  $\geq$  130 mg/dL.
- Within each cohort, 10 unique subjects will be randomized 4:1 to receive up to a total daily dose of 50 mg TLC-2716 (N = 8) or PTM (N = 2) for either 1 day (as in Part A) or 14 days (as in Part B).

The frequency of dosing (QD or BID in MAD cohorts) and fasting versus fed status (in SAD or MAD cohorts) may also be modified versus Parts A and B. If dosing is administered in the fed state, standard meal conditions may also be modified at sponsor discretion. QD doses will be administered in the morning following a standard meal, and BID doses will be administered after a standard morning meal and evening snack, with the second dose administered 12 hours

(± 10 minutes) after the morning dose. Once determined, dose level, duration of dosing, frequency of dosing, and meal conditions will remain consistent within a cohort. For any MAD cohort in Part C with BID dosing, both morning and evening doses must be administered on Day 14.

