### **MAD Cohorts in Parts B and C:**

Day 1: Pre-dose ( $\leq 10$  minutes prior to dosing), 0.25, 0.5, 1, 1.5, 2, 2.5, 3, 3.5, 4, 6 and 12 hours post-dose

Days 3, and 7: Pre-dose ( $\leq 10$  minutes prior to dosing), 2, and 4 hours post-dose

Day 14: Pre-dose ( $\leq 10$  minutes prior to dosing), 0.25, 0.5, 1, 1.5, 2, 2.5, 3, 3.5, 4, 6, 12, 24, 48, and 72 hours post-dose

***If in any MAD cohort in Part C, BID administration is evaluated, PK assessments should be performed at the following time points.***

Day 1: Pre-dose morning ( $\leq 10$  minutes prior to dosing), 0.25, 0.5, 1, 1.5, 2, 2.5, 3, 3.5, 4, 6, and 12 hours post morning dose (12-hour time point collected prior to evening dose)

Days 3 and 7: Pre-dose morning ( $\leq 10$  minutes prior to dosing), 2, and 4 hours post morning dose

Day 14: Pre-dose morning ( $\leq 10$  minutes prior to dosing), 0.25, 0.5, 1, 1.5, 2, 2.5, 3, 3.5, 4, 6, and 12 hours post morning dose (12-hour time point collected prior to evening dose), 12.5, 13, 14, 16, 18, 24, 48, and 72 hours post-dose

Every effort should be made to collect PK samples at the scheduled time point.

Plasma concentrations of TLC-2716 (and its metabolites, as applicable) will be determined and other PK parameters evaluated, as appropriate. Sampling time points may be modified by the sponsor based on emerging data and assay feasibility.

For all cohorts, a single PK sample will be collected at the ET visit, if applicable.

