## **8. PHARMACOKINETIC ANALYSIS**

### **8.1.1. Data Handling**

All PK analyses will use the PK Analysis Set. Plasma concentrations and plasma PK parameters will be listed and summarized for TLC-2716 and its metabolites (TLC-6665, TLC-7255), as applicable using descriptive statistics by treatment and PK Day (as applicable) for each cohort. Plasma concentration versus time curves will also be presented.

Plasma concentrations that are below the limit of quantification (BLQ) will be treated as zero for calculation of descriptive statistics. When all concentrations are BLQ for a timepoint, the mean BLQ concentrations will be presented as BLQ, and the SD and CV will be reported as not applicable.

For PK parameter calculation, BLQ values prior to a quantifiable concentration will be treated as zero. BLQ values between 2 quantifiable concentrations, or in the terminal phase will be set as missing. If consecutive BLQ concentrations in the terminal phase are followed by quantifiable concentrations, those concentrations after consecutive BLQ concentrations will be treated as missing.

No missing data imputation will be performed.

Missing concentrations will be treated as missing from the descriptive statistics and PK parameter calculations.

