### 8.1.3. Plasma Pharmacokinetic Parameters

The plasma concentration-time data for TLC-2716 and its metabolites will be analyzed by noncompartmental analysis using Phoenix® WinNonLin® Version 8.3.4 or higher (Certara USA, Inc., Princeton, NJ). The following single- and multiple-dose PK parameters will be calculated for TLC-2716 and its metabolites as applicable based on actual times, where data permit:

| PK Parameter   | Definition                                                                                                |
|----------------|-----------------------------------------------------------------------------------------------------------|
| $C_{max}$      | Maximum observed plasma concentration                                                                     |
| $t_{max}$      | Time of maximum observed concentration                                                                    |
| $t_{last}$     | Time of last measurable concentration                                                                     |
| $AUC_{last}$   | AUC from time 0 to the last quantifiable concentration, calculated using the linear trapezoidal rule      |
| $AUC_{inf}$    | AUC from time 0 extrapolated to infinity, calculated using the linear trapezoidal method                  |
| $AUC_{tau}$    | Area under the concentration-time curve for one dosing interval (tau). (Day 1 and Day 14 for MAD cohorts) |
| $t_{1/2}$      | Apparent terminal elimination half-life, calculated as: $\ln(2) / K_{el}$                                 |
| CL/F           | Apparent total body clearance, calculated as: $Dose / AUC_{inf}$                                          |
| $V_z/F$        | Volume of distribution during the terminal phase, calculated as: $Dose / [K_{el} * AUC_{inf}]$            |
| $AR_{C_{max}}$ | Accumulation ratio based on $C_{max}$ , calculated as: $C_{max} (Day 14) / C_{max} (Day 1)$               |
| $AR_{AUC}$     | Accumulation ratio based on $AUC_{tau}$ , calculated as: $AUC_{tau} (Day 14) / AUC_{tau} (Day 1)$         |

In addition to the above PK parameters, which will be listed and summarized, the following parameters will also be listed to document the selection of data points used to estimate  $t_{1/2}$  using non-compartmental procedures:

| PK Parameter     | Definition                                                                                                                             |

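### If a twice-daily cohort is run in Part C, the SAP's Day 14 PK rules do not separate the morning and evening doses, which can inflate Cmax, AUCtau and their accumulation ratios and makes AUClast a two-dose quantity

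*Combined protocol and SAP*

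**What the plan says.** **Dosing and sampling.** Part C may use once-daily or BID dosing, but it is optional: "The sponsor, in consultation with the investigator, may choose not to initiate any or all adaptive cohorts if deemed unnecessary". Protocol 3.1.3 adds: "For any MAD cohort in Part C with BID dosing, both morning and evening doses must be administered on Day 14". Under protocol 6.5.1, BID Day 1 sampling ends at "6, and 12 hours post morning dose (12-hour time point collected prior to evening dose", so it sees one dose. Day 14 sampling continues on the same clock past the evening dose: "12-hour time point collected prior to evening dose), 12.5, 13, 14, 16, 18, 24, 48, and 72 hours post-dose". SAP 8.1.2 does not list the 12.5-18 h samples, but a footnote to the MAD schedule in the SAP appendix sends BID timing back to protocol 6.5.

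**Parameters.** SAP 8.1.3 defines Cmax as the highest observed concentration, with no interval attached. AUClast is "AUC from time 0 to the last quantifiable concentration, calculated using the linear trapezoidal rule". Only AUCtau is tied to one dosing interval. ARCmax and ARAUC are the Day 14 to Day 1 ratios of Cmax and AUCtau, and SAP 8.1.6 models the same two parameters.

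**BLQ handling for parameter calculation (SAP 8.1.1).** A BLQ value that precedes a quantifiable one is set to zero. Then: "BLQ values between 2 quantifiable concentrations, or in the terminal phase will be set as missing". For quantifiable values that follow consecutive terminal-phase BLQs, "those concentrations after consecutive BLQ concentrations will be treated as missing". No rule resets at a new dose.

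**The concern.** The rules suit a record with one dose in it. On BID Day 14 there are two, with four consequences.

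1. Day 14 Cmax is a maximum over two peaks and Day 1 Cmax over one, so ARCmax is not like for like.
2. Day 14 AUClast includes the evening dose whenever the evening samples are kept.
3. A BLQ sample at 12 h lies between quantifiable morning and evening values. Once it is dropped, the next retained point is 12.5 h, on the rising limb of the evening dose, and the AUCtau partial area is drawn up towards it.
4. If 6 h and 12 h are both BLQ, the sentence on embedded values keeps the evening profile, while the sentence on consecutive terminal BLQs can delete it. The SAP does not say which governs.

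Cmax, AUCtau and AUClast are primary endpoints (protocol 8.1.2) and enter the power model (SAP 8.1.4.1). Cmax and AUCtau carry the accumulation analysis. Subjects in one cohort could have a one-dose or a two-dose AUClast according to whether their troughs were quantifiable.

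**Working it through.** The plan states no figure on this point, so there is none to reproduce. The check applies the SAP rules literally to the protocol's BID sampling times.

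**Inputs from the documents:** sampling times (protocol 6.5.1), linear trapezoid and parameter definitions (SAP 8.1.3), BLQ rules (SAP 8.1.1), tau = 12 h.

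**Assumptions, because the documents give no values:** one-compartment oral model, identical morning and evening doses, ka 2/h, half-life 0.5-3 h, LLOQ 1-10% of Cmax, AUCtau to 12 h by linear interpolation where a later sample exists, within-subject CV 20-40%.

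**AUCtau, one case in full.** Each dose contributes C(t) = ka/(ka - ke) x (exp(-ke t) - exp(-ka t)), with ke = ln 2 / half-life. Take a half-life of 1 h and LLOQ 1% of Cmax.

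- Cmax = 0.570, so LLOQ = 0.0057. C(6) = 0.0239 (quantifiable), C(12) = 0.0004 (BLQ), C(12.5) = 0.5194.
- True AUC0-12 = 1.443. Trapezoid over 0-6 h = 1.407.
- With 12 h dropped, the interpolated value at 12 h is 0.0239 + (6/6.5) x (0.5194 - 0.0239) = 0.481.
- Area over 6-12 h = 6 x (0.0239 + 0.481)/2 = 1.516.
- AUCtau = 1.407 + 1.516 = 2.923, which is 2.923/1.443 = 2.03 times true.
- Day 1 has no later sample to bridge to and gives 1.441, so ARAUC = 2.923/1.441 = 2.03 against a true 1.00.

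**Selected cases:**

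| Half-life, LLOQ | BLQ before evening dose | Evening data | AUCtau / true | ARAUC (true) | AUClast / true AUC0-12 |
|---|---|---|---|---|---|
| 0.75 h, 1% | 12 h | kept | 2.26 | 2.27 (1.00) | 3.37 |
| 1 h, 1% | 12 h | kept | 2.03 | 2.03 (1.00) | 3.10 |
| 2 h, 5% | 12 h | kept | 1.60 | 1.63 (1.02) | 2.51 |
| 3 h, 10% | 12 h | kept | 1.42 | 1.53 (1.08) | 2.21 |
| 1 h, 5% | 6 h, 12 h | kept | 2.53 | 2.56 (1.00) | 3.52 |
| 1 h, 5% | 6 h, 12 h | deleted | 0.99 | 1.00 (1.00) | 0.89 |
| 3 h, 5% | none | kept | 1.03 | 1.08 (1.08) | 2.06 |

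Over the whole grid:

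- Only 12 h BLQ: AUCtau is 1.42-2.26 times true. Moving ka between 1 and 3/h gives a similar range.
- 6 h and 12 h both BLQ, evening data kept: 2.53-4.14 times.
- 6 h and 12 h both BLQ, evening data deleted: AUCtau 0.97-0.99 of true, ARAUC 1.00, AUClast 0.89-0.97 of the one-interval AUC.
- 12 h quantifiable: AUCtau 1.03-1.04 times true, ARAUC unbiased.

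**Cmax.** For two independent lognormal peaks with equal medians and no accumulation, the geometric mean of the larger is exp(s/sqrt(pi)) times that of one, with s = sqrt(ln(1 + CV^2)).

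- CV 20%: s = 0.198, ratio 1.12
- CV 30%: s = 0.294, ratio 1.18
- CV 40%: s = 0.385, ratio 1.24

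At CV 30%, an evening peak 0.8 of the morning peak gives 1.08, and one of 0.5 gives 1.01.

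**The case against.** **The zero rule.** The first BLQ sentence could be read to cover the 12 h sample, since a quantifiable value follows it. Set to zero, it does no harm: in the worked case the 6-12 h area is 6 x 0.0239/2 = 0.072, and AUCtau is (1.407 + 0.072)/1.443 = 1.02 times true. This is not the natural reading. The next sentence specifically governs BLQs between two quantifiable values, and it would have no work to do if the zero rule reached them. The wording still leaves room for two answers.

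**Likelihood.** A reader might infer that the AUCtau inflation is to be expected, because the protocol reports a profile "with undetectable plasma levels 2-4 hours after dosing". That statement is preclinical. Carried over to humans, it points to 6 h being BLQ as well as 12 h, which is the case where the SAP's two sentences conflict and where deletion leaves AUCtau and accumulation about right. A BLQ trough is plausible, but the documents do not say how often it would occur.

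**Accumulation.** A reader might infer that every branch spoils accumulation. It does not. AUClast is not used there, the deletion branch gives nearly correct ratios, and a quantifiable 12 h sample protects AUCtau.

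**Dose proportionality.** A reader might infer that the slope must be distorted. Adding an illustrative 25 mg BID cohort to the five once-daily doses, with a true slope of 1.00, gives 1.09 for AUClast against unit dose and 0.90 for AUCtau against daily dose. AUCtau against unit dose and AUClast against daily dose both give 1.00. The SAP calls the regressor only dose and mandates no mismatched pairing, so what stands is that the pairing is undefined.

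**Cmax.** Equal peaks may be generous to the concern. The evening dose follows a snack, and its peak is sampled more sparsely than the morning's. This stands, and it is why the range runs down to about 1%.

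**Scope.** Part C is optional and BID is one choice within it. Part B and all single-dose cohorts are untouched.

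**Conclusion.** The concern holds for a BID multiple-dose cohort, if one is run. Followed as written, the SAP does more than omit detail; it can produce wrong Day 14 values.

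- **ARCmax** is biased upward by about 12-24% for CV 20-40% if morning and evening peaks are exchangeable, and by close to nothing if evening peaks are much lower.
- **AUCtau and ARAUC** are inflated when the 12 h sample is BLQ and dropped: AUCtau by about 1.4 to 2.3 fold when 6 h is quantifiable, and more if 6 h is also BLQ and the evening data are kept.
- **AUClast** covers two doses, about 2.1 to 3.4 times the one-interval AUC while 6 h is quantifiable. This affects exposure summaries and dose proportionality.
- **With 6 h and 12 h both BLQ**, the rules conflict. Deletion costs the evening profile and makes AUClast inconsistent between subjects, but leaves AUCtau and accumulation about right.

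The mechanisms follow from the text. The sizes rest on an assumed one-compartment model and on assumed half-life, absorption rate, LLOQ and CV, so they are ranges and not predictions. An experienced pharmacokineticist might split the record unprompted, but the SAP does not require it.

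**What to change.** Add to SAP 8.1.1 and 8.1.3, for BID cohorts:

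1. Apply the BLQ rules within each dosing interval, so that a pre-evening BLQ is neither an embedded value nor a trigger for deleting evening samples.
2. Derive the Day 14 Cmax, tmax and AUCtau used for accumulation from the 0-12 h samples only, matching Day 1.
3. Derive evening-interval parameters and Kel separately, from samples taken after the evening dose.
4. In the power model (SAP 8.1.4.1), pair AUCtau and Cmax with the dose per administration, and leave the two-dose Day 14 AUClast out of that model for BID cohorts.

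Under the same assumptions, treating 0-12 h as its own profile brings Day 14 AUCtau to 0.97-1.00 of true and ARAUC to 1.00-1.07 against a true 1.00-1.08, and removes the second-peak effect from ARCmax.

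The cost is a few lines of SAP text and interval settings in the noncompartmental software. No samples or subjects are added, and nothing changes if no BID cohort is run.

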### **8.1.2. Plasma Pharmacokinetic Concentrations**

Part A – SAD:

Day 1: Blood samples for PK analysis of concentrations of TLC-2716 and its metabolites in plasma will be collected at the following timepoints: predose ( $\leq 10$  minutes prior to dosing) and 0.25, 0.5, 1, 1.5, 2, 2.5, 3, 3.5, 4, 6, 12, 24, 48, and 72 hours postdose.

Part B – MAD and Part C – Adaptive SAD and/or MAD:

Day 1: Blood samples for PK analysis of concentrations of TLC-2716 and its metabolites in plasma will be collected at the following timepoints: predose ( $\leq 10$  minutes prior to dosing) and 0.25, 0.5, 1, 1.5, 2, 2.5, 3, 3.5, 4, 6, 12, and 24 hours postdose.

Days 3 and 7: Predose ( $\leq 10$  minutes prior to dosing) and 2 and 4 hours postdose.

Day 14: Blood samples for PK analysis of concentrations of TLC-2716 and its metabolites in plasma will be collected at the following timepoints: predose ( $\leq 10$  minutes prior to dosing) and 0.25, 0.5, 1, 1.5, 2, 2.5, 3, 3.5, 4, 6, 12, 24, 48, and 72 hours postdose.

Individual plasma concentrations of TLC-2716 and its metabolites will be presented in data listings and summarized separately using descriptive statistics (N [number of subjects], n [non-missing values within the population], arithmetic mean, SD, CV%, median, minimum, and maximum) by study part, treatment, cohort, day, as applicable, and nominal time point. Mean ( $\pm$  SD) plasma concentrations of TLC-2716 and its metabolites will be plotted by study part, dose, cohort, day, as applicable, and nominal time on both linear and semi-logarithmic scales.

### 8.1.3. Plasma Pharmacokinetic Parameters

The plasma concentration-time data for TLC-2716 and its metabolites will be analyzed by noncompartmental analysis using Phoenix® WinNonLin® Version 8.3.4 or higher (Certara USA, Inc., Princeton, NJ). The following single- and multiple-dose PK parameters will be calculated for TLC-2716 and its metabolites as applicable based on actual times, where data permit:

| PK Parameter   | Definition                                                                                                |
|----------------|-----------------------------------------------------------------------------------------------------------|
| $C_{max}$      | Maximum observed plasma concentration                                                                     |
| $t_{max}$      | Time of maximum observed concentration                                                                    |
| $t_{last}$     | Time of last measurable concentration                                                                     |
| $AUC_{last}$   | AUC from time 0 to the last quantifiable concentration, calculated using the linear trapezoidal rule      |
| $AUC_{inf}$    | AUC from time 0 extrapolated to infinity, calculated using the linear trapezoidal method                  |
| $AUC_{tau}$    | Area under the concentration-time curve for one dosing interval (tau). (Day 1 and Day 14 for MAD cohorts) |
| $t_{1/2}$      | Apparent terminal elimination half-life, calculated as: $\ln(2) / K_{el}$                                 |
| CL/F           | Apparent total body clearance, calculated as: $Dose / AUC_{inf}$                                          |
| $V_z/F$        | Volume of distribution during the terminal phase, calculated as: $Dose / [K_{el} * AUC_{inf}]$            |
| $AR_{C_{max}}$ | Accumulation ratio based on $C_{max}$ , calculated as: $C_{max} (Day 14) / C_{max} (Day 1)$               |
| $AR_{AUC}$     | Accumulation ratio based on $AUC_{tau}$ , calculated as: $AUC_{tau} (Day 14) / AUC_{tau} (Day 1)$         |

In addition to the above PK parameters, which will be listed and summarized, the following parameters will also be listed to document the selection of data points used to estimate  $t_{1/2}$  using non-compartmental procedures:

| PK Parameter     | Definition                                                                                                                             |
|------------------|----------------------------------------------------------------------------------------------------------------------------------------|
| $K_{el}$         | Elimination rate constant                                                                                                              |
| Number points    | Number of data points used to estimate $K_{el}$ ; a minimum of 3 data points must be used, and $C_{max}$ must not be included.         |
| $K_{el}$ lower   | Lower bound used for the estimation of $K_{el}$                                                                                        |
| $K_{el}$ upper   | Upper bound used for the estimation of $K_{el}$                                                                                        |
| Span             | Number of elapsed half-lives over which $K_{el}$ is estimated, calculated as $(K_{el} \text{ upper} - K_{el} \text{ lower}) / t_{1/2}$ |
| $R_{sq}$         | $r^2$ , the coefficient of determination (goodness of fit statistic)                                                                   |
| % $AUC_{extrap}$ | Percentage of $AUC_{inf}$ due to extrapolation                                                                                         |

Plasma PK parameters for TLC-2716 and its metabolites will be presented in data listings and summarized separately using descriptive statistics (N, n, arithmetic mean, SD, CV%, geometric mean, geometric CV%, median, minimum, and maximum) by study part, treatment, cohort, and

day, as applicable.  $t_{\max}$ ,  $t_{1/2}$ , and  $t_{\text{last}}$  will be summarized using the descriptive statistics median, minimum, and maximum only.

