#### 6.5.1. Plasma PK Collection

##### SAD Cohorts in Parts A and C:

PK sampling will occur relative to the morning dosing of TLC-2716 or PTM at the following time points for each cohort:

Day 1: Pre-dose ( $\leq 10$  minutes prior to dosing), 0.25, 0.5, 1, 1.5, 2, 2.5, 3, 3.5, 4, 6, 12, 24, 48, and 72 hours post-dose

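### The linear trapezoidal rule in SAP 8.1.3 can overstate AUC, and understate CL/F and Vz/F, by up to about 9% if drug or metabolite is still quantifiable at 12 h or later; AUCtau has no stated rule

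*Combined protocol and SAP*

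**What the plan says.** SAP 8.1.3 defines AUClast as "AUC from time 0 to the last quantifiable concentration, calculated using the linear trapezoidal rule" and AUCinf as "AUC from time 0 extrapolated to infinity, calculated using the linear trapezoidal method". AUCtau is defined only as "Area under the concentration-time curve for one dosing interval (tau). (Day 1 and Day 14 for MAD cohorts)", with no integration rule. CL/F is dose divided by AUCinf, and Vz/F is dose divided by the product of Kel and AUCinf. Neither document mentions a logarithmic rule for the declining phase.

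SAP 8.1.2 gives the sampling times for Part A and for Day 14 of the multiple-dose cohorts as "0.25, 0.5, 1, 1.5, 2, 2.5, 3, 3.5, 4, 6, 12, 24, 48, and 72 hours postdose"; protocol 6.5.1 agrees. SAP 8.1.1 adds a rule that matters here: "BLQ values between 2 quantifiable concentrations, or in the terminal phase will be set as missing". The area is therefore summed only as far as the last quantifiable sample (Tlast).

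The only evidence on how long plasma stays quantifiable is nonclinical. Protocol 1.2.3 reports "undetectable plasma levels 2-4 hours after dosing".

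**The concern.** The linear rule joins consecutive concentrations with a straight line. On an exponential decline that line lies above the curve, and the excess grows with the width of the gap measured in half-lives. Sampling is close up to 4 h, so little is lost there. After that the plan applies the same rule across gaps of 2, 6, 12, 24 and 24 h.

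Protocol 8.1.2 lists AUClast, AUCinf, AUCtau, CL/F and Vz/F among the primary endpoints, and the AUCs feed the power model for dose proportionality (protocol 8.7, SAP 8.1.4.1). A higher dose of the same profile stays quantifiable longer and so can enter wider gaps. The error could then differ between doses as well as being positive on average.

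**Working it through.** The plan states no figure for AUC error, so there is nothing of its own to reproduce. The sampling times, the integration rule and the BLQ rule come from the documents. Absorption rate (ka), half-life and LLOQ are not given, so they are assumed below and shown over ranges.

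**One gap.** For a gap of width D on a mono-exponential decline with k = ln 2 / half-life, the linear rule overstates that interval's area by (kD/2)·coth(kD/2) − 1.

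| Half-life | 6 h gap | 12 h gap | 24 h gap |
|---|---|---|---|
| 2 h | 34% | 115% | 316% |
| 4 h | 9% | 34% | 115% |
| 8 h | 2% | 9% | 34% |
| 24 h | 0.3% | 1% | 4% |

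The large entries fall in intervals that hold little of the total area, so they are not AUC errors.

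**One whole profile.** Take C(t) = exp(−kt) − exp(−ka·t), ka 2/h, half-life 4 h, Tlast 24 h, in arbitrary units. Then C(6) = 0.3535, C(12) = 0.1250 and C(24) = 0.0156.

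- 6-12 h: linear (0.3535 + 0.1250)/2 × 6 = 1.436; true 1.319.
- 12-24 h: linear (0.1250 + 0.0156)/2 × 12 = 0.844; true 0.631.
- AUClast: linear 5.498 against true 5.181, or +6.1%. Linear-up/log-down gives 5.160, or −0.4%.
- AUCinf: linear 5.588 against true 5.271, or +6.0%. CL/F is then off by 1/1.060 − 1 = −5.7%. With linear-up/log-down the AUCinf error is −0.4%.

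For this profile the linear AUCinf error by Tlast is −0.2% (6 h), +2.0% (12 h), +6.0% (24 h), +8.0% (48 h) and +8.0% (72 h). It rises and then levels off.

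**Range of profiles.** Assumptions: one compartment, ka 0.4-6/h (above 1.2k), half-life 0.5-36 h, Cmax/Clast at most 1000. The AUClast error is:

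| Tlast | Linear | Linear-up/log-down |
|---|---|---|
| 4 h | −2.9% to −0.3% | −5.1% to −0.3% |
| 6 h | −2.3% to +0.4% | −4.4% to −0.4% |
| 12 h | −1.3% to +6.8% | −2.1% to −0.2% |
| 24 h | −0.6% to +9.4% | −1.9% to −0.1% |
| 48 h | +0.4% to +9.1% | −1.5% to −0.1% |
| 72 h | +0.7% to +8.0% | −1.1% to −0.1% |

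With the true terminal slope used for extrapolation, the largest AUCinf overstatement is also +9.4%. CL/F is then understated by at most 1 − 1/1.094 = 8.6%; the same factor applies to Vz/F if Kel is right.

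**Dose proportionality.** A simple guide: if the error ran from 0% at 0.5 mg to +8% at 20 mg, the slope would move by ln(1.08)/ln(40) = 0.021. Under exact proportionality at the planned doses, with and without 50 mg (ka 2/h, half-life 1-12 h, Cmax/LLOQ of 5-100 at 0.5 mg), the fitted AUCinf slope is 1.000 to 1.018 with the linear rule and 1.000 with linear-up/log-down. For AUClast the worst case is 1.146 linear and 1.128 linear-up/log-down. So 0.128 of that 0.146 is truncation at Tlast, which changing the rule does not remove.

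**AUCtau.** If AUCtau over 24 h were also linear, with a 24 h sample available on both days (ka 2/h, half-life 1-24 h), it would be overstated by 0.4% to 6.9%. The overstatement is nearly equal on Day 1 and at steady state, so the accumulation ratio hardly moves (1.071 true and 1.071 linear at a 6 h half-life).

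**The case against.** The strongest reply is that the wide gaps may never be used. The nonclinical evidence points to plasma clearing within hours, and terminal BLQ values are set to missing. If Tlast is 4-6 h, only the 2 h gap is entered. The linear error is then small and mostly slightly negative, and linear-up/log-down does a little worse because a log trapezoid never exceeds a linear one on a falling interval. On a narrower set of profiles (ka 1.0-1.5/h, 0.25 h lag, half-life 1.5-8 h) with Tlast 6 h, the linear error is −0.55% to about 0% and the linear-up/log-down error is −1.4% to −0.6%. This stands, and it is why the point is conditional. It does not dispose of it: the plan samples to 72 h, doses over a 100-fold range up to 50 mg, and analyses two metabolites whose kinetics are not described. The late samples count only when they are quantifiable, which is when the linear rule errs.

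A reader might infer that AUC will be overstated and CL/F understated whatever happens. The documents do not support that, for the reason just given. Nor does the error always grow with Tlast: it plateaus, and for a bi-exponential profile (1 h and 24 h phases, 3% slow component) the AUClast error is 1.66%, 1.64% and 1.97% at 12, 24 and 48 h.

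A reader might also infer that the dose-proportionality conclusion is at risk. With 8 active subjects at each of five doses, the 90% CI half-width for the slope is about 0.04, 0.06, 0.08 and 0.11 at assumed CVs of 20%, 30%, 40% and 60%. A shift of about 0.02 lies inside all of them.

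Three further replies are fair. The linear rule is pre-specified and contradicts nothing else in the plan. Twice-daily cohorts have extra Day 14 samples between 12 and 18 h, which break up the 12 h gap. The sponsor may also modify sampling times on emerging data.

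**Conclusion.** The point holds as a minor, conditional specification issue. If parent or metabolite is quantifiable at 12 h or later, the linear rule can overstate AUClast and AUCinf by up to about 9% and understate CL/F and Vz/F by a similar amount. With Tlast at 6 h or earlier there is no overstatement of consequence (at most +0.4% in the profiles examined). The effect on the AUCinf slope is about 0.02 at most, and accumulation ratios are essentially unaffected. The missing rule for AUCtau is a plain gap whatever the half-life.

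The direction across a wide gap on an exponential decline is a matter of geometry. The sizes rest on one-compartment kinetics and on assumed half-lives, absorption rates and quantitation limits, none of which the documents supply.

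**What to change.** In SAP 8.1.3, replace the linear rule for AUClast and AUCinf with the linear-up/log-down trapezoidal method (linear while concentrations rise, logarithmic while they fall). State the same rule for AUCtau on Day 1 and Day 14. Apply it to TLC-2716 and its metabolites, and settle it before any AUC is calculated for the final analysis, so that the choice does not depend on the data.

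The cost is one setting in the PK software and one line of SAP text, with no new samples. Reported AUCs become slightly lower. The price is a small extra understatement when the last quantifiable sample is at 4-6 h: roughly 1 percentage point or less in most of the narrower set of profiles (at most 1.3), and up to about 2 at the extremes of the wider range. With Tlast at 12 h or later, the remaining error in the profiles examined is −2.1% to −0.1%.
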